### Follow-up criteria and participant timeline

Patients will continue to receive intervention until one of following events occurs:Positivity of any of the cultures taken from the CVC hubsRecovery of neutropenia: > 500 neutrophils/μLRemoval of the catheter for any causeEpisode of CRBSINeed to use the CVC for the administration of a medication in continuous infusion that cannot be stopped for any reasonDischarge from the haematology ward for any reason, despite not having recovered from the neutropeniaDeath

Once the patient concludes the study for any of the previous events, a 30-day follow-up will take place to assess possible complications until that date. The intervention will be stopped in patients in whom significant colonisation of a CVC hub is detected, but they will continue to be followed-up to check whether they develop CRBSI. Whenever the catheter is removed on suspicion of infection, the hubs and tip of the catheter will be sent for microbiological culture.

A patient will be considered to have discontinued the study when the patient withdraws the informed consent, dies, or is lost to follow-up. The trial will be considered finished when all the recruited participants have completed the 30-day follow-up period. Figure 1 shows the participant timeline of the study.

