### Definitions

Significant colonisation of any catheter hub will be defined as the presence of any microbial growth in the qualitative culture of the swabs. CRBSI will be defined as the detection of growth of bacteria or fungi in at least one blood culture obtained from a peripheral vein, associated with clinical signs and symptoms of infection (e.g. fever, chills, and/or hypotension), and no apparent source for BSI other than the CVC. In the case of common skin-colonising microorganisms, such as CNS, two positive sets of blood cultures will be necessary to make the diagnosis of CRBSI. CRBSI attributed to luminal colonisation will be defined as the isolation of identical organisms from the catheter hub and from cultures of separate percutaneously drawn blood specimens; the organism’s identity will be proven by molecular typing for patients with BSI due to CNS. Overall, the 30-day case-fatality rate will be defined as death by any cause within the 30 days following the end of the intervention.

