#### Secondary endpoints

The assessment of the secondary endpoints will be performed as follows:Incidence of CRBSI: swabs of the insertion site and catheter hubs as well as blood cultures (at least one from a peripheral vein) will be obtained when CRBSI is suspected. In the case of catheter removal, two 5-cm segments, a proximal subcutaneous segment and the tip, will be sampled using the sterile technique for culture. The incidence of CRBSI and the CRBSI attributed to luminal colonisation will be calculated for each group. The differential time to positivity will not be used to diagnose CRBSI. The development of CRBSI will be assessed during intervention and up to 30 days after the last intervention. The rate of CRBSI will be presented as the number of episodes of CRBSI per 1000 admission daysCVC removal: whenever it is necessary to remove the CVC because of occlusion, thrombosis, dislodgement or suspicion and/or documentation of infection, the tip is going to be sent for culture to the microbiology department, and the reasons for removal will be annotated in the data collection form and the database by the participating investigators. The need for CVC removal will be assessed during intervention and up to 30 days after the last interventionAdverse reactions: any adverse reaction potentially associated with the administration of the lock solution will be annotated in the data collection form and the database by the participating investigators. Adverse events will be identified and classified according to the severity and the potential relationship with the lock solution. They will be assessed during the interventionOverall (30-day) case-fatality rate: all patients included in the study will be followed up for a total of 30 days after the end of the intervention by the participating investigators. Death by any cause will be annotated in the data collection form and the database

The research nurse in charge of the study will visit the patients daily in order to collect all the data related to the study. Also, the nurse will assess the potential development of any adverse event, and will collect all the information in the database. Adverse events will be classified according to their severity and causality. Only the serious adverse events, and those considered to be related to the use of the product of the study will be reported to the study promoter and to the regulatory authorities.

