### Sample size

According to our previous experience [26], we estimated that around 20% of patients in the control group will present positive cultures of the catheter hubs. A reduction of this figure to 5% in the taurolidine-citrate-heparin group would be clinically relevant. To detect a 15% difference between groups with a power of 80%, it would be necessary to include 135 patients in the study. Considering the possibility of a loss of 10% of cases, the final sample should be 150 patients.

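### The 30-day mortality clock starts at the end of the intervention, an event the lock itself can change, and it is not settled whether a death on the lock counts

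*Protocol article*

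**What the plan says.** Under Definitions, the "30-day case-fatality rate will be defined as death by any cause within the 30 days following the end of the intervention". Under Secondary endpoints the same anchor is used for mortality follow-up: "all patients included in the study will be followed up for a total of 30 days after the end of the intervention". For CRBSI, that section says "The development of CRBSI will be assessed during intervention and up to 30 days after the last intervention", and catheter removal has the same window.

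The end of the intervention is set under Follow-up criteria and participant timeline: "Patients will continue to receive intervention until one of following events occurs". The list that follows includes any positive hub culture, neutrophil recovery, catheter removal, CRBSI, an unavoidable continuous infusion, discharge from the ward, and death. Then "Once the patient concludes the study for any of the previous events, a 30-day follow-up will take place".

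Under Statistical analysis, CRBSI, removal and death are compared as frequencies. Kaplan-Meier curves and a log-rank test are planned for colonisation and BSI only. CRBSI is also to be reported per 1000 admission days (Secondary endpoints). No section sets a window of fixed length from randomisation.

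**The concern.** A randomised comparison of event frequencies needs a common time origin and a common length of observation. Here the origin for mortality, and the close of the CRBSI and removal windows, depend on when the intervention ends. Hub colonisation ends it, and the lock is meant to reduce hub colonisation. If it does, taurolidine patients stay on the lock longer and their observation ends later after randomisation.

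Mortality has a second problem. The CRBSI and removal windows expressly include the intervention period. The mortality definition does not, and death is itself a stopping event. A death on the lock therefore falls exactly on the boundary, and the article does not say on which side. Those deaths bear directly on the safety of the lock, and in a trial of 150 patients a few of them can change the mortality comparison.

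**Working it through.** The article gives no follow-up length by arm, so there is no stated figure to reproduce. The size has to be derived.

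**Inputs from the article.** Control colonisation 20%: "around 20% of patients in the control group will present positive cultures of the catheter hubs". Taurolidine 5%: "A reduction of this figure to 5% in the taurolidine-citrate-heparin group would be clinically relevant". Tail of 30 days after the intervention. 150 patients, hence 75 per arm. CRBSI at 2.66 per 1000 line-days (Discussion), used only as an illustration.

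**Assumptions.** Planned lock period L of 7, 14 or 28 days (the article says only that neutropenia is expected to exceed 7 days). Constant hazard of hub positivity that reaches 20% or 5% by day L. Other stopping events equal between arms. Mortality of 5% or 10% per 30 days.

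**Step 1: the two readings of the mortality definition.**
- On-lock deaths excluded: each arm has 30 days, but the clock starts at an arm-dependent time, only patients alive at the end of the intervention are at risk, and on-lock deaths drop out.
- On-lock deaths included: nothing is lost, but the window is lock time plus 30 days and is unequal.

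Only one of these can apply. Neither gives 30-day mortality from randomisation.

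**Step 2: window length if the lock period is included.** Mean time on lock = p × L / (−ln(1 − p)). For L = 14: control 0.20 × 14 / 0.2231 = 12.55 days; taurolidine 0.05 × 14 / 0.0513 = 13.65 days. Add 30 days to each.

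| L (days) | Lock, control | Lock, taurolidine | Window, control | Window, taurolidine | Difference | Ratio |
|---|---|---|---|---|---|---|
| 7 | 6.27 | 6.82 | 36.27 | 36.82 | 0.55 | 1.015 |
| 14 | 12.55 | 13.65 | 42.55 | 43.65 | 1.10 | 1.026 |
| 28 | 25.10 | 27.29 | 55.10 | 57.29 | 2.2 | 1.040 |

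If every positive culture came at day 2, the difference would be (0.20 − 0.05) × (L − 2) = 0.75, 1.8 or 3.9 days (ratios 1.021, 1.043, 1.074). A simulation with gamma-distributed lock lengths (means 8, 12 and 20 days) and a 2-day culture lag gave ratios of 1.012, 1.020 and 1.032.

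**Step 3: effect on frequencies when the hazard of the event is equal in both arms.** Risk = 1 − exp(−hazard × mean window).
- CRBSI, control v taurolidine: 9.2% v 9.3% (L = 7), 10.7% v 11.0% (L = 14), 13.6% v 14.1% (L = 28).
- Death, L = 14: 7.02% v 7.19% at 5% per 30 days, and 13.88% v 14.21% at 10%. Per 75 patients that is 75 × 0.0017 = 0.13 and 75 × 0.0033 = 0.25 of a death.

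**Step 4: deaths on the lock.** With hazard h = −ln(1 − m)/30, where m is the 30-day mortality, on-lock deaths per arm = 75 × (1 − exp(−h × lock time)). For L = 14 this gives 1.59 (control) and 1.73 (taurolidine) at 5%, and 3.23 and 3.51 at 10%. In the control arm at 5%, total deaths to the end of the window are 75 × 0.0702 = 5.3, so 1.59/5.3 = 30% of them turn on how the boundary is read. Over L = 7 to 28 and 5% to 10% mortality, on-lock deaths range from 0.8 to 6.9 per arm.

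**Step 5: after the change.** With a fixed 30 days from randomisation, the planned difference between arms is 0 days by construction.

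**The case against.** The strongest reply is that the imbalance is negligible. It is a fraction of a death per arm on a secondary endpoint, and it works against taurolidine. If the lock changes none of the stopping events, the windows are equal, so an inert lock gains nothing. Nor can CRBSI, removal or death shorten observation of that same endpoint, since it has already occurred. All of this stands as to size. Colonisation, however, still moves the window for all three endpoints.

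CRBSI is also partly protected, by the rate per 1000 admission days and by the log-rank analysis of BSI. That stands too. The protection is partial, because the planned frequency comparison remains and removal and death have no time-based analysis.

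Several stronger readings are tempting but unsupported:
- A reader might infer that on-lock deaths precede the mortality window and are excluded. The text does not say so. Death ends the intervention, so these deaths lie on the boundary, and the article says that death by any cause will be recorded. The defect is that their inclusion is unsettled.
- A reader might hold that on-lock deaths are lost and mortality windows are unequal at once. Step 1 shows that these exclude each other.
- A reader might infer that deaths would be imputed, because "A patient will be considered to have discontinued the study when the patient withdraws the informed consent, dies, or is lost to follow-up" and missing data are to be multiply imputed. No section treats death as missing, and it is defined as an endpoint.
- A reader might make much of the shift between end of the intervention and last intervention. With locks every 48 to 72 h these could be up to about 3 days apart if read literally, but the follow-up section describes a single 30-day follow-up. This needs only tidier wording.

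**Conclusion.** The point holds in limited form. The mortality clock has a post-randomisation, arm-dependent origin, and the definition leaves on-lock deaths unsettled. Removal and the crude CRBSI frequency are observed over windows that a working lock would lengthen. At the plan's own colonisation rates the mean imbalance is about 0.5 to 2 days (1.5% to 4%; up to 7% if all colonisation came at day 2), slightly against taurolidine. The unsettled deaths weigh more: roughly 1.6 to 3.5 per arm for a 14-day lock period and 5% to 10% mortality. Lock period, shape of the hazard and mortality are assumptions, since the article gives none of them. The direction and the ambiguity follow from the text alone. The point does not touch the primary endpoint, but it should be corrected because the correction for mortality is nearly free.

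**What to change.** **Mortality.** Define the endpoint as death from any cause within 30 days of randomisation, counting deaths during the intervention. The end of the intervention cannot precede randomisation, so planned follow-up already covers this for every patient. Keep the figure for 30 days after the end of the intervention as supportive, and state that it includes on-lock deaths.

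**CRBSI and catheter removal.** Keep the full observation period and compare the arms by time to event from randomisation, extending the planned Kaplan-Meier and log-rank analysis to removal, with death as a competing event. Do not cut these endpoints at day 30 from randomisation. In the scenarios above that would drop about 6 to 27 days of a 36- to 57-day mean window, including follow-up meant to detect CRBSI after colonisation.

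**Wording.** Use one term for the follow-up anchor throughout.

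**Cost.** The changes are to wording in Definitions, Secondary endpoints and Statistical analysis, with no new visits. Dates of death and removal must be recorded, which Data collection does not list explicitly. Deaths after day 30 from randomisation move to the supportive analysis. Beyond day 30, censoring in the time-to-event analyses still follows the stopping event, so the dependence is reduced there but not removed.

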### Study outcomes and endpoint assessment

#### Primary endpoint

For the assessment of the primary endpoint (bacterial colonisation rate of the CVC hubs), swabs of the inner surfaces of the catheter hubs will be obtained by the nursing personnel before randomisation and three times weekly (approximately every 48-72 h) thereafter for culture, until the end of the intervention. All swabs are made of viscose, and only the swab of the catheter insertion site has a transport media (Stuart media). One swab is used for each lumen The cultures of the collected swabs will be processed in the microbiology department. The results of the cultures will be reviewed by the participating investigators and will be written down in the data collection form and in the specific database.

#### Secondary endpoints

The assessment of the secondary endpoints will be performed as follows:Incidence of CRBSI: swabs of the insertion site and catheter hubs as well as blood cultures (at least one from a peripheral vein) will be obtained when CRBSI is suspected. In the case of catheter removal, two 5-cm segments, a proximal subcutaneous segment and the tip, will be sampled using the sterile technique for culture. The incidence of CRBSI and the CRBSI attributed to luminal colonisation will be calculated for each group. The differential time to positivity will not be used to diagnose CRBSI. The development of CRBSI will be assessed during intervention and up to 30 days after the last intervention. The rate of CRBSI will be presented as the number of episodes of CRBSI per 1000 admission daysCVC removal: whenever it is necessary to remove the CVC because of occlusion, thrombosis, dislodgement or suspicion and/or documentation of infection, the tip is going to be sent for culture to the microbiology department, and the reasons for removal will be annotated in the data collection form and the database by the participating investigators. The need for CVC removal will be assessed during intervention and up to 30 days after the last interventionAdverse reactions: any adverse reaction potentially associated with the administration of the lock solution will be annotated in the data collection form and the database by the participating investigators. Adverse events will be identified and classified according to the severity and the potential relationship with the lock solution. They will be assessed during the interventionOverall (30-day) case-fatality rate: all patients included in the study will be followed up for a total of 30 days after the end of the intervention by the participating investigators. Death by any cause will be annotated in the data collection form and the database

The research nurse in charge of the study will visit the patients daily in order to collect all the data related to the study. Also, the nurse will assess the potential development of any adverse event, and will collect all the information in the database. Adverse events will be classified according to their severity and causality. Only the serious adverse events, and those considered to be related to the use of the product of the study will be reported to the study promoter and to the regulatory authorities.

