### Data collection

The following data will be collected: sex, age, type of underlying disease, other comorbidities, date of hospital admission, HSCT, type and date of HSCT, immunosuppressive therapy, concomitant medication, duration of neutropenia, type of CVC, days from CVC insertion to inclusion in the study, use of prophylactic antibiotics or antifungal agents, systemic antibiotic therapy, number of catheter locks per episode, results of the cultures of the hubs and CVC insertion site, any episodes of infection, episodes of CRBSI, the need for CVC removal and reason, development of complications, adverse reactions, overall case-fatality rate, CRBSI attributable case-fatality rate, and date of discharge.

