### Statistical analysis

The analysis of the data will be carried out during the last 6 months of the project when all fieldwork has been completed. The database will then be analysed using the stepwise logistic regression model of the R software (R v. 3.2.5). The analyses will be made by intention-to-treat (all patients randomised who have a primary endpoint available). To handle missing data multiple imputation will be done under the missing at random assumption.

For the analysis of the primary endpoint, the frequency of colonisation of the CVC hubs in both treatment groups will be compared. For the analysis of the secondary endpoints, the frequency of CRBSI will be compared between the two groups, as well as the need for CVC removal for any cause and overall case-fatality rate (30 days). Exploratory subgroup analyses will be conducted by underlying haematological condition (leukaemia, autologous HSCT, and allogeneic HSCT) and by centre. Due to the fact that a patient could have been included twice, the potential impact of independence violation will be assessed repeating the main analysis using patient as a cluster.

The statistical analysis will be carried out using a Student’s *t* test and a chi-square test. A multivariate analysis will be performed to verify the absence of confusion by other variables. In addition, free time of colonisation of the catheter and BSI will be analysed using Kaplan-Meier curves, and they will be compared between both groups by means of the log-rank test (Mantel-Cox test). A value of *p* = 0.05 will be considered statistically significant.

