Patients with cancer who have a CVC implanted are at special risk of developing CRBSI. Infection rates of 2.66 per 1000 line-days have been found in adult haematology/oncology and bone marrow transplant units [37]. Recently, lock solution technique as a preventive strategy for CRBSI in patients with cancer has been systematically reviewed [19]. The great majority of studies were performed in paediatric patients (10 studies), and only three were carried out in the adult population. Vancomycin was the most frequently studied solution because the great majority of infections are caused by Gram-positive bacteria. The results of vancomycin studies were variable; some studies showed a reduction of CRBSI in paediatric patients with cancer [23, 25], while others failed to do so [24]. Moreover, Carratalà et al. [26] demonstrated a significant reduction of CRBSI in neutropenic haematological patients using vancomycin as lock solution in the single study carried out in adults. Nevertheless, the widespread use of prophylactic antibiotics as catheter lock solutions may contribute to the development of antibiotic-selective pressure and resistance. In addition, the emergence of Gram-negative bacteria as an important cause of CRBSI raises the doubt about the current utility of vancomycin. Furthermore, three studies investigating ethanol as a lock solution in paediatric and adult patients with cancer showed discordant results [20–22]. Moreover, relatively frequent adverse effects have been reported with the use of ethanol-based solutions, which limits its use for this purpose [21, 22].

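### The descriptive CRBSI rate counts episodes up to 30 days after the last lock but divides by admission days, so numerator and denominator cover different periods

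*Protocol article*

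**What the plan says.** Three parts of the protocol article bear on this rate.

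- **Numerator** (Secondary endpoints): "The development of CRBSI will be assessed during intervention and up to 30 days after the last intervention".
- **Denominator** (same item): "The rate of CRBSI will be presented as the number of episodes of CRBSI per 1000 admission" days. The article does not define admission days further.
- **End of intervention** (Follow-up criteria and participant timeline): the events that end the locks include catheter removal for any cause and discharge from the ward. Then: "Once the patient concludes the study for any of the previous events, a 30-day follow-up will take place". That follow-up is not limited to time in hospital or time with a catheter.

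The Definitions section requires that there be "no apparent source for BSI other than the CVC" for an episode to count as CRBSI. In the Statistical analysis section the planned comparisons are different measures: "the frequency of CRBSI will be compared between the two groups", and "free time of colonisation of the catheter and BSI will be analysed using Kaplan-Meier curves", with a log-rank test. The Discussion gives a literature rate on another scale: "Infection rates of 2.66 per 1000 line-days have been found in adult haematology/oncology and bone marrow transplant units".

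**The concern.** An incidence rate can be interpreted only if events and person-time come from the same period at risk. Here they do not, in two or possibly three ways.

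1. A patient discharged with the catheter in place (PICC carriers are eligible) can have a CRBSI at home. The episode is counted, but the days at home are not.
2. A patient whose catheter is out but who stays in hospital adds days on which a new catheter infection can hardly arise.
3. If admission days run from the hospital admission date, which is a collected item, days before randomisation are added too. Patients are randomised after chemotherapy, and CRBSI is assessed only from the intervention onward, so no counted episode can fall on those days.

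CRBSI is the first-listed secondary endpoint, and this is the only rate per unit of time that the article specifies for it. Readers and meta-analysts would be likely to extract it and set it beside catheter-day rates from other studies.

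**Working it through.** The article states no expected CRBSI rate, episode count, length of stay or catheter dwell time, so there is no planned figure to reproduce. The arithmetic below shows how the stated formula behaves.

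**Inputs from the document:** a 30-day window after the last lock; 150 patients randomised 1:1, hence 75 per arm; a cited rate of 2.66 per 1000 line-days. **Assumed:** 4 episodes per arm, L = 10 to 20 lock days in hospital, and a fraction f of the 30 follow-up days spent in hospital. Other assumed stays and catheter times are stated where used.

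**Step 1: episodes after discharge (upward effect).** Rate per admission day = 1000 × 4 / [75 × (L + 30f)]. Rate per day observed = 1000 × 4 / [75 × (L + 30)]. Their ratio is (L + 30) / (L + 30f).

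| f | L = 10 | L = 20 |
|---|---|---|
| 0 | 5.33 vs 1.33, ratio 4.0 | 2.67 vs 1.07, ratio 2.5 |
| 0.5 | 2.13 vs 1.33, ratio 1.6 | 1.52 vs 1.07, ratio 1.43 |
| 1 | 1.33 vs 1.33, ratio 1.0 | 1.07 vs 1.07, ratio 1.0 |

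This mismatch disappears only when the whole window is spent in hospital.

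**Step 2: against the cited scale.** Suppose the true rate is 2.66 per 1000 line-days and each patient has 30 catheter-days (assumed). The displayed rate is 2.66 × 30 / A for A admission days: 5.32 (A = 15), 3.99 (A = 20), 3.19 (A = 25), 2.66 (A = 30).

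**Step 3: hospital days without a catheter (downward effect).** With 24 admission days and 18 catheter-days (assumed), and all episodes arising while the catheter is in, the factor is 18 / 24 = 0.75. A true 2.66 would then appear as 2.66 × 0.75 = 2.00. Days before randomisation act in the same direction.

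**Step 4: difference between arms from length of stay alone.** Take 4 of 75 patients (5.3%) with one episode in each arm, and mean stays of 20 and 25 days (assumed). The rates are 1000 × 4 / (75 × 20) = 2.67 and 1000 × 4 / (75 × 25) = 2.13. Their ratio is 20 / 25 = 0.80, although the proportions with CRBSI are identical.

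**The case against.** The strongest reply is that this rate is only for presentation. The Statistical analysis section compares CRBSI frequency between groups and BSI-free time by log-rank. Neither uses admission days, and no rate ratio is planned. This stands. A reader might infer that the treatment comparison for CRBSI is biased, but the document does not support that. The ratio of 0.80 in Step 4 is what someone would get by dividing the two displayed rates, not the result of a planned analysis.

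A reader might also infer that the reported rate will be wrong, or too high by a known factor. The document does not support that either. Post-discharge episodes push the rate up; catheter-free and pre-randomisation hospital days push it down. The article gives none of the quantities needed to net them.

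The CRBSI definition, which leaves the catheter as the only apparent source, makes episodes long after removal unlikely. That limits the numerator but does not remove catheter-free days from the denominator.

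The exact meaning of admission days could be left to a fuller document, so the point about pre-randomisation days is conditional. The mismatch between a window that can outlast the stay and a denominator of admission days is fixed in the article itself.

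The 2.66 per 1000 line-days is background. It is neither a planned comparator nor a sample-size input. It shows only that the article uses another scale when it cites the literature.

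Finally, a catheter-day denominator has a weakness of its own. Catheters may be removed on suspicion of infection, so a clock that stops strictly at removal could drop episodes confirmed just afterwards. Removal is also itself a post-randomisation endpoint, so censoring there may be informative. Both points stand and shape the fix.

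**Conclusion.** The point holds as a defect in one descriptive secondary measure. As written, the CRBSI rate mixes an episode window that can run past discharge and catheter removal with a denominator of admission days. It is not an incidence of catheter infection, it can differ between arms through length of stay alone, and it cannot be set beside line-day rates.

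Its size is illustrative only. The factor is 1.0 to 4.0 relative to days observed, for 10 to 20 in-hospital lock days and follow-up spent anywhere from wholly in hospital to wholly outside it. It is 0.75 relative to catheter-days in the example with catheter-free hospital time. The net direction is not fixed by the document. The primary endpoint, the CRBSI frequency comparison and the log-rank analysis are untouched.

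**What to change.** In the Secondary endpoints section, present CRBSI per 1000 catheter-days at risk. Count these from randomisation (or first lock) to the earliest of first CRBSI, catheter removal, death, loss to follow-up or the end of the 30-day window, whether in or out of hospital. Count episodes over the same period, and include those confirmed from cultures taken at removal or within a short, pre-specified time of it.

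Keep the per-patient frequency comparison as planned; it does not depend on censoring at removal. An admission-day rate may be kept as a supplement if both its episodes and its days are limited to time in hospital after randomisation.

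The change of text is small; the main cost is data. The Data collection section lists "the need for CVC removal and reason" but no removal date. That date is needed for every patient whose catheter was removed, including those discharged with the catheter in place. Recruitment began on 1 January 2013 and was due to end on 30 June 2018, so unless the case record form already holds the date, it would have to be recovered retrospectively for many patients before database lock.
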